#### Population and clinical history data

2.11.4

The descriptive statistics for each applied group are presented, and the continuous variables will be analyzed with 2-sided *t* test or Wilcoxon rank-sum test according to the satisfaction of normality assumption. Categorical variables will be analyzed to determine whether the cells with an expected frequency of <5 exceed 20% followed by Pearson chi-squared test or Fisher exact test.

### Assessment

2.12

#### Primary assessment

2.12.1

The primary endpoint will be the number of mature oocytes harvested at 10 weeks from baseline. The descriptive for each applied group will be presented and analyzed with the 2-sample *t* test or Wilcoxon rank-sum test depending on the satisfaction of normality.

#### Secondary assessment

2.12.2

1.AFC and AMH level at 8 weeks from baselineThe descriptive for each applied group will be presented and analyzed with the 2-sample *t* test or2.DASS-42 score at 4 and 8 weeks compared to baselineThe descriptive for each applied group will be presented and analyzed with the 2-sample *t* test or Wilcoxon rank-sum test depending on the satisfaction of normality.

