### Power calculation

2.4

This study is a randomized, open phase IV, exploratory clinical trial to assess the efficacy and safety of acupuncture in adult women diagnosed with POR after induction of ovulation. The primary efficacy endpoint will be the number of mature oocytes collected at approximately 10 weeks. The sample size in this study will be calculated by referring to the results of a transcutaneous electrical acupoint stimulation (TEAS) study performed by Zheng et al, because there is no related study, although the same acupuncture study results should be referred to. According to Zheng et al, the number of mature oocytes was counted as 2.38 ± 1.55 in the control group and 4.87 ± 3.47 in the TEAS treatment group. The results of the experimental group were assumed to be the effect of TEAS, and the standard deviation (Stdev) was assumed to be the Stdev of 3.47. Based on the results of this study, 31 subjects were included to secure 80% of power with 5% to the bilateral significance and 1:1 of the dispensing ratio. If the dropout rate is 10%, 35 subjects in each group will be recruited.

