### Recruitment, randomization

2.5

This study is open phase; therefore, random assignment codes will be assigned using the block randomization method. This will be done using SAS (Version 9.3, SAS Institute, Cary, NC), by a statistician who is not directly related to this clinical study. The statistician will distribute the randomization code to the person in charge of the clinical trial institution before commencing the clinical trial.

Subjects who will be enrolled in the study and who will meet the inclusion/exclusion criteria will be assigned to each application group in a randomized sequential envelope according to the random assignment number. This randomization number will be used as the study participant identification code during the trial. The entire process of the study will be directed by the authorized clinical research organization (CRO), CROcent Corporation, Seoul, Korea.

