#### Baseline

2.7.2

(1)The baseline is the second day of menstruation. On the second day, information will be collected by performing history confirmation, previous drugs, vital signs, anti-Müllerian hormone (AMH) test, antral follicle count (AFC) using ovarian ultrasound, random assignment, and evaluation with the depression anxiety stress scales (DASS) 42.(2)One-time after-screening randomization is performed at a ratio of 1:1 eligible subjects on the second day of menstruation.Arm 1: IVF-ET after acupuncture.Arm 2: IVF-ET.

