#### Inclusion criteria

2.8.1

The subjects should meet all the following criteria.

1.Sex: female2.Age: 20 to 45 years3.Women who have voluntarily signed a written consent to participate in the trial4.Women who have had infertility for more than 1 year or who have been diagnosed with infertility in a medical institution5.Women who have been diagnosed with POR (including at least 2 of the following criteria)a.Advanced maternal age (≥40 years) or any other risk factor for PORb.A previous POR (≤3 oocytes with a conventional stimulation protocol)c.An abnormal ovarian reserve test (AMH < 0.5–1.1 ng/mL or total AFC < 5–7 follicles)6.Women who have the ability and willingness to take the test during the clinical trial period

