#### Secondary outcome

2.10.2

At 8 weeks from the baseline of the treatment period, patients will be assessed for AFC and AMH. The DASS-42 score will be measured at 4 and 8 weeks from baseline.

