#### General analysis

2.11.3

The statistical analysis will be conducted by blinded professional statisticians. Unless otherwise specified, all data will be based on a 2-sided test at a significance level of 5%. The continuous variable gives the number of observation, the mean ± stdev and the median (minimum values, maximum values), while the categorical variable gives the frequency and percentage. If missing values are found in continuous validation variables, they will be analyzed using the last observation carried forward method. At this time, the results before applying the clinical trial device (control randomized) will not be replaced by the results after applying the clinical trial device. If a categorical validation variable has a missing value, it will be considered a failure and included in the analysis. Safety assessment variables will not replace missing values.

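### Week-8 AFC and AMH are compared without the baseline values already collected: a valid test that gives up precision on two secondary endpoints

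*Protocol article*

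**What the plan says.** All references are to the protocol article.

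- **Baseline (2.7.2).** The second day of menstruation is the baseline visit. Its list of procedures includes "anti-Müllerian hormone (AMH) test, antral follicle count (AFC) using ovarian ultrasound, random assignment", and "randomization is performed at a ratio of 1:1 eligible subjects on the second day of menstruation". Both measures therefore exist for each woman on the day she is allocated.
- **Follow-up (2.10.2).** There is one later measurement of each: "At 8 weeks from the baseline of the treatment period, patients will be assessed for AFC and AMH".
- **Analysis (2.12.2).** "AFC and AMH level at 8 weeks from baselineThe descriptive for each applied group will be presented and analyzed with the 2-sample" t test, followed by the word 'or', at which point the sentence stops and the DASS-42 item begins. Section 2.12.1 uses parallel wording for the primary endpoint and names the Wilcoxon rank-sum test as the alternative, so that is probably what was lost. It would ignore the baseline too.
- **Meaning of 'from baseline'.** In 2.10.1, 2.10.2 and 2.12.1 the phrase gives timing. It is used that way even for oocytes, which have no baseline value. It does not define a change score.
- **Other routes to adjustment.** Section 2.5 says that "random assignment codes will be assigned using the block randomization method" and names no stratification factor. Section 2.11.4 compares baseline variables between arms but does not connect the result to any adjustment. The shown text has no covariate, change score or stratum for AFC or AMH.

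**The concern.** AFC and AMH are the trial's only ovarian-reserve endpoints, and so its evidence on whether acupuncture alters reserve before stimulation. If a woman's week-8 value is related to her value eight weeks earlier, part of the spread between women at week 8 was present before treatment. A two-sample test counts that part as noise, although the data needed to remove it are in hand.

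Two things are at stake. A real change in reserve is more likely to be missed than it need be. And if the arms happen to differ in AMH or AFC at entry, part of that difference carries through to the week-8 comparison with nothing in the analysis to take it out.

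This is not a detail left to a plan that is not shown: the article names both the endpoint and the test.

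**Working it through.** **Inputs from the article.** Two-sided 5% level (2.11.3: "all data will be based on a 2-sided test at a significance level of 5"); 1:1 allocation; 31 evaluable women per arm, 35 recruited (2.4).

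**Input that is assumed.** The correlation rho between baseline and week 8. The documents give no value, so a range is shown.

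**1. The plan's own figure.** Section 2.4 takes the primary endpoint from a cited study: "the number of mature oocytes was counted as 2.38 ± 1.55 in the control group and 4.87 ± 3.47 in the TEAS treatment group". The difference is 4.87 − 2.38 = 2.49 and the SD is set at 3.47.

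n per arm = 2 × (1.96 + 0.842)² × 3.47² / 2.49² = 30.5, rounded up to 31; 31 / 0.9 = 34.4, rounded up to 35.

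Both stated numbers reproduce. No sample size or power is stated for AFC or AMH.

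**2. What the raw test can detect.** With 31 per arm (noncentral t, 60 df), a two-sample t test of the week-8 level has 80% power for a difference of 0.723 SD and 50% power for 0.506 SD.

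**3. What ANCOVA does with the same difference.** The residual SD becomes SD × √(1 − rho²), so residual variance falls by rho². One degree of freedom is lost (59 instead of 60).

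| rho | fall in residual variance | ANCOVA power where raw test has 80% | ANCOVA power where raw test has 50% |
|---|---|---|---|
| 0.3 | 9% | 83.5% | 54% |
| 0.5 | 25% | 89.9% | 62% |
| 0.6 | 36% | 93.8% | 69% |
| 0.7 | 49% | 97.5% | 78% |

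With 35 per arm the pattern is the same. In sample-size terms, the raw test would need about 31 / (1 − rho²) per arm to match ANCOVA: 31 / 0.75 = 41 at rho 0.5 and 31 / 0.51 = 61 at rho 0.7.

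**4. Why not a change score.** Its SD is SD × √(2(1 − rho)), which equals the raw SD at rho 0.5 and exceeds it below that. For the 0.723 SD difference its power is 66% at rho 0.3, 80% at 0.5 and 95% at 0.7. It is below ANCOVA at each of these values.

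**5. Chance imbalance.** The standard error of the baseline difference between arms is √(2/31) = 0.254 SD. A difference above 0.4 SD in either direction has probability 2 × (1 − Φ(0.4 / 0.254)) = 2 × (1 − Φ(1.575)) = 11.5%.

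Given a baseline difference b (in SD) and no treatment effect, the raw test statistic is approximately normal with mean m = rho × b / 0.254 and SD s = √(1 − rho²). Its conditional false-positive rate is 1 − Φ((1.96 − m)/s) + Φ((−1.96 − m)/s).

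- b = 0.4, rho 0.5: m = 0.787, s = 0.866, rate 8.9%.
- b = 0.4, rho 0.7: m = 1.102, s = 0.714, rate 11.5%.
- b = 0, rho 0.5: 2 × (1 − Φ(1.96 / 0.866)) = 2.4%.
- b = 0, rho 0.7: 2 × (1 − Φ(1.96 / 0.714)) = 0.6%.

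Averaged over all imbalances that randomisation can produce, the rate is 5%.

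**The case against.** **The planned test is not wrong.** In a 1:1 randomised trial an unadjusted comparison has an overall type I error of 5%, and chance imbalance is already part of that 5%. A reader might infer from the conditional rates of 9% to 11.5% that the plan inflates false positives. It does not: those rates apply to an imbalance of exactly 0.4 SD and are offset by rates below 5% when the arms are balanced. This stands in full. What remains is lost precision, and an analysis that cannot respond to the imbalance actually seen.

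**The gain rests on an assumed rho.** This also stands. Below rho 0.3 the gain is trivial. One might argue that rho must be high because the entry criteria admit women by several routes, but the article does not establish that. Two of three criteria are needed, and one of them is "An abnormal ovarian reserve test (AMH < 0.5–1.1 ng/mL or total AFC < 5–7 follicles". Women who enter through that criterion have a restricted range of at least one measure, which tends to lower rho; women who enter on the other two need not. The criteria do not settle the matter either way.

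**The analysis sentence is incomplete.** True, but the named t test has no baseline term, and neither would the rank-sum test that most likely follows.

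**A fuller protocol or analysis plan may add adjusted models.** Possibly. The article still states the unadjusted test as the analysis, and that stated choice is what is questioned here.

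**DASS-42.** A reader might extend the point to the DASS-42 analysis, described in 2.12.2 as relative to baseline, and fault it as an inefficient change score. The wording does not fix the model, so the text does not support that criticism. Nor does the order of items in the baseline list show that any measurement was taken after allocation was known.

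**Conclusion.** The point holds as a matter of efficiency. The article fixes an unadjusted two-sample comparison of week-8 AFC and AMH although the same measures are taken on the randomisation day.

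Measured at a difference for which the raw test has 80% power, the power given up is about 4 points at rho 0.3, 10 at 0.5, 14 at 0.6 and 17 to 18 at 0.7. These figures assume 31 evaluable women per arm, roughly normal residuals, a linear relation to baseline and equal spread in the two arms. Rho is an assumption, and the recommendation matters little if it is 0.3 or lower.

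The planned test is valid, the endpoints are secondary, and the trial is declared exploratory. The primary endpoint, its analysis and the sample size are untouched. The change should be made because it is nearly free, not because a main conclusion depends on it.

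**What to change.** In section 2.12.2, complete the broken sentence and state that:

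- week-8 AFC and week-8 AMH are each analysed by ANCOVA, with arm as factor and the randomisation-day value of the same measure as covariate;
- if residuals are clearly non-normal, the log scale or a rank-based ANCOVA is used;
- the adjusted difference is reported with its 95% confidence interval (a ratio if the log scale is used);
- the unadjusted two-sample test is kept as a supportive analysis.

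This should be fixed before outcome data are seen, so that adjustment is not chosen in response to an imbalance found in the baseline comparisons of 2.11.4.

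The cost is one degree of freedom per model and the need for an observed baseline value in each woman analysed. No visit, test or participant is added.

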#### Other assessment

2.12.3

(1) The in vitro fertilization rate of retrieved oocytes at 10 weeks from baseline

The frequency and percentage of the applied group will be presented and analyzed with Pearson chi-squared test or Fisher exact test.

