### Study design

2.2

This study will include only an IVF-ET trial and an IVF-ET trial after acupuncture treatment in the form of RCTs. Seventy patients will by enrolled and randomly assigned into either of the 2 groups of the trial. The trial will be conducted at the infertility center in Pusan National University (PNU, Busan, Republic of Korea, Trial protocol version: KI-17-D-001 Version 2.0, August 8, 2017). The study subjects will be required to be diagnosed as having POR. Participants will be divided into 2 groups: IVF-ET single treatment group, and acupuncture and IVF-ET combined treatment group. The entire flow chart of the study is shown in Fig. 1. The study subjects will be required to participate in a 15-week trial involving 16 acupuncture treatments during a period of approximately 2 months before ovulation induction for oocyte retrieval.

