#### Other outcomes

2.10.3

At 10 weeks from baseline, the in vitro fertilization rate of retrieved oocytes will be assessed.

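### The fertilisation rate of retrieved oocytes is to be tested with a plain chi-squared or Fisher test; if the oocyte is the unit, as it reads, the test ignores clustering within women and does not hold 5%

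*Protocol article*

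**What the plan says.** Section 2.10.3 (Other outcomes) introduces the variable: "At 10 weeks from baseline, the in vitro fertilization rate of retrieved oocytes will be assessed". Section 2.12.3 (Other assessment) repeats it as "The in vitro fertilization rate of retrieved oocytes at 10 weeks from baseline" and fixes the analysis: "The frequency and percentage of the applied group will be presented and analyzed with Pearson chi-squared test or Fisher exact test". Neither section says in words whether the oocyte or the woman is counted, and neither mentions several oocytes coming from one woman.

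Three other places bear on the point.

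- Section 2.2 (Study design) makes the woman the unit of randomisation: "Seventy patients will by enrolled and randomly assigned into either of the 2 groups of the trial".
- Section 2.4 (Power calculation) cites planning data that show how many oocytes a woman may contribute: "the number of mature oocytes was counted as 2.38 ± 1.55 in the control group and 4.87 ± 3.47 in the TEAS treatment group".
- Section 2.11.3 (General analysis) sets the error level, "Unless otherwise specified, all data will be based on a 2-sided test at a significance level of 5" per cent, and a rule for missing categorical data: "If a categorical validation variable has a missing value, it will be considered a failure and included in the analysis".

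**The concern.** A rate of retrieved oocytes has oocytes in its denominator. Oocytes from one woman share her age, the sperm source, the stimulation cycle and the laboratory handling, so their fertilisation results are correlated. Pearson's chi-squared and Fisher's exact test on pooled oocytes assume independence. With positive correlation the standard error is too small, and a few women with many oocytes can drive an apparent benefit or harm.

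The missing-data rule fits the oocyte reading poorly as well. A woman with no retrieved oocytes has nothing that could fail to fertilise, and a woman who drops out has an unknown number of oocytes. Counting either as failure means inventing a denominator.

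What is at stake is the one listed outcome that speaks most directly to oocyte quality after retrieval, which the Discussion says the trial will evaluate.

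**Working it through.** **The plan's own figure.** The only sample size is for the primary endpoint. With a difference of 4.87 − 2.38 = 2.49, SD 3.47, two-sided 5% and 80% power, n = 2 × (1.960 + 0.842)² × 3.47² / 2.49² = 30.5, so 31 per arm; 31 / 0.9 = 34.4, so 35 with dropout. Both figures reproduce. They are used here only to fix the number of women at 31 per arm.

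**Inputs from the document.** Oocytes per woman: mean 2.38, SD 1.55 (control) and mean 4.87, SD 3.47 (treated), from section 2.4. These are mature oocytes, standing in for retrieved oocytes. Retrieved oocytes are at least as many, so the inflation at a given ICC could be somewhat higher than shown.

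**Assumptions.** The ICC is varied because the document gives none. The simulation also needs a fertilisation rate, assumed to be 65%; the formula below does not use it.

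**Formula.** For mean m and SD s, the size-weighted cluster size is k = m(1 + s²/m²) = m + s²/m.

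- Control: k = 2.38 + 1.55²/2.38 = 3.389.
- Treated: k = 4.87 + 3.47²/4.87 = 7.342.

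The design effect per arm is D = 1 + (k − 1) × ICC. The variance of the difference is inflated by V = (D₁/m₁ + D₂/m₂) / (1/m₁ + 1/m₂). The actual false-positive rate is 2 × [1 − Φ(1.96/√V)].

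**Example, ICC 0.1.** D₁ = 1 + 2.389 × 0.1 = 1.239 and D₂ = 1 + 6.342 × 0.1 = 1.634. V = (1.239/2.38 + 1.634/4.87) / (1/2.38 + 1/4.87) = 1.369. The rate is 2 × [1 − Φ(1.96/1.170)] = 9.4%.

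**Chi-squared false-positive rate at nominal 5%, by formula:**

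| Assumed ICC | Control vs treated counts | Control counts in both arms | Treated counts in both arms |
|---|---|---|---|
| 0.05 | 7.2% | 6.4% | 8.8% |
| 0.1 | 9.4% | 7.8% | 12.5% |
| 0.2 | 13.7% | 10.7% | 19.3% |
| 0.3 | 17.7% | 13.5% | 25.0% |
| 0.5 | 24.5% | 18.6% | 33.7% |

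**Check by simulation.** Beta-binomial fertilisation within woman, negative binomial oocyte counts, 31 women per arm, 20,000 runs. For the control-versus-treated pair, chi-squared rejects in 7.2%, 9.3%, 13.4%, 17.9% and 24.8% of runs at the five ICCs, in line with the formula.

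**Fisher.** From smaller simulations of the same pair, so less precise: about 5.5 to 6.5% at ICC 0.05, 8% at 0.1, 15 to 16% at 0.3 and 22 to 23.5% at 0.5. With no correlation it rejects in only about 3.7%, and at ICC 0.02 it stays at or under 5%.

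**Clustered alternative.** A ratio test with variance clustered by woman rejects in about 5 to 6%.

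**ICC needed for a given inflation.** For the control-versus-treated pair, chi-squared reaches 10% at an ICC of about 0.11 and 25% at about 0.52. With control counts in both arms these are about 0.18 and 0.80; with treated counts in both arms, about 0.07 and 0.30.

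**The case against.** **The unit is not stated.** A per-woman variable, such as at least one fertilised oocyte, would also suit a frequency and percentage, would fit the missing-as-failure rule better, and would have no clustering. An analysis plan that is not shown may settle this. That stands as a reason to word the point conditionally. It does not remove it: both sections name a rate of retrieved oocytes, no per-woman fertilisation variable is defined anywhere, and the protocol itself fixes the test.

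**The size rests on an unknown ICC.** This stands. A reader might infer that the error rate is two to five times nominal. The document does not support that as a fact, because it needs an ICC of about 0.11 to 0.52 with the quoted counts. Section 2.8.1 includes a previous yield of at most 3 oocytes among the qualifying criteria, so small clusters are plausible, and these lower the inflation.

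**Fisher is conservative.** This also stands. A reader might infer that any positive correlation inflates the error. That is true of chi-squared, but not of Fisher at a very small ICC.

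**The outcome ranks low.** It is neither primary nor secondary, the trial is called exploratory, and no decision or sample size depends on it. This limits the importance, but an exploratory label does not make the p-value valid.

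**Conclusion.** The point holds in conditional form. If the oocyte is the unit, which is the natural reading, the stated test assumes an independence that does not exist and does not hold the two-sided 5% level. For chi-squared the direction is certain for any positive ICC. The size is not: over assumed ICCs of 0.05 to 0.5 and the three count scenarios it runs from about 6.4% to 34%, and Fisher is somewhat lower. These figures rest on the quoted mature-oocyte counts applying to retrieved oocytes and on the assumed ICCs.

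Severity is low to moderate. A reader should not infer that the trial's main result is affected: the primary endpoint is a count per woman, and its test and sample size do not depend on this analysis.

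**What to change.** 1. State the unit of analysis for the fertilisation rate in section 2.12.3.
2. If it is the oocyte, replace chi-squared/Fisher with a comparison of fertilised over retrieved oocytes that allows for clustering by woman: a logistic GEE, or a ratio estimator with robust variance, either with a small-sample correction.
3. Say that this rate exists only for women with at least one retrieved oocyte. That subset is formed after randomisation, and acupuncture is hypothesised to change oocyte yield, so the comparison is not fully protected by randomisation. Report beside it the number of fertilised oocytes per randomised woman, counting 0 where none were retrieved.
4. Exempt the oocyte-level rate from the missing-as-failure rule in section 2.11.3, because the number of missing oocytes is undefined.

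The cost is a few sentences of text and a few lines of code. The confidence interval will be wider, reflecting the information actually available.
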